#### Safety and reporting of serious adverse events

In this study, adverse events will be defined as any treatment-related medical event, including any adverse and unexpected signs, symptoms, or illnesses associated with the treatment. Adverse events will be evaluated according to the Standard for General Terminology for Adverse Events (V4.03) [21]. Within 24 h after the occurrence of adverse events, the researchers and relevant experts will evaluate and classify the events and address them in a timely manner according to the condition. We will collect, evaluate, and report any spontaneously described adverse events that occur among the participants. Adverse event data regarding the severity of the occurrence, duration (signs and symptoms) of the adverse reactions, and how to resolve them (or not) during treatment will be recorded. If the participants experience serious adverse events, they will be reported to the principal investigator and the Ethics Committee of West China Hospital of Sichuan University (IEC), and it will be decided whether the blinding should be removed and whether the participants should withdraw from the study.

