**Methods:**

A randomised single-blind parallel-controlled trial is proposed for this project, and patients who meet the inclusion criteria will be divided into a test group and a control group, with 39 patients in each group. The experimental group will be treated with modified ultrasonic scalpel haemorrhoidectomy, and the control group will be treated with the Milligan-Morgan operation. The effectiveness of modified ultrasonic scalpel haemorrhoidectomy for haemorrhoids will be objectively evaluated, including the incision healing time and the time for patients to return to normal activities, postoperative complications, evaluations of anal function 3 months and 6 months after surgery, an evaluation of quality of life 6 months after surgery, and an evaluation of the patient satisfaction rate 6 months after surgery. The safety assessment will consider all adverse and serious adverse events associated with the study treatment.

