### Objectives

A randomised controlled blind study is planned to objectively evaluate the efficacy of modified ultrasonic scalpel haemorrhoidectomy in the treatment of haemorrhoids. The healing time of the incision, the time taken for patients to return to normal activities, postoperative complications, evaluations of anal function 3 months and half a year after surgery, an evaluation of the quality of life at half a year after surgery, and an evaluation of the patients’ satisfaction rates half a year after surgery will be measured.

To assess safety, the incidence of adverse events (AEs) and serious adverse events (SAEs) between the two study groups will be compared to show the potential risks for patients.

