#### Randomisation and blinding

Participants will be randomly assigned equally to the two study groups with the use of simple randomisation, in which a third-party statistician will use computer software to generate pseudorandom numbers. Only the clinical data manager will have access to the random number table in the computer. Subjects will be enrolled by a research assistant in the order of enrolment time. Allocation will be made by the clinical data manager using the random number table. The statistician will be blinded to the allocation of subjects during the statistical analysis.

Since the surgical operator and the observer must know which group each subject has been assigned to, they cannot be blinded. The study has a single-blind design in which the investigators will be aware of the surgical procedures used in the different trial groups, but the participants will be unaware of them.

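### Relatedness is written into the adverse-event definition while assessors know the arm, so the comparison of events outside the systematically assessed outcomes is open to differential attribution

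*Protocol article*

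**What the plan says.** Under Safety and reporting of serious adverse events, the protocol article fixes the definition: "adverse events will be defined as any treatment-related medical event". The same sentence repeats the condition: "including any adverse and unexpected signs, symptoms, or illnesses associated with the treatment". The Methods paragraph of the abstract carries the restriction into the assessment: "The safety assessment will consider all adverse and serious adverse events associated with the study treatment".

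On ascertainment, the safety section says: "We will collect, evaluate, and report any spontaneously described adverse events that occur among the participants". Within 24 hours of an event, "the researchers and relevant experts will evaluate and classify the events". The attributes listed for recording are severity, duration and resolution. Relatedness is not among them.

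Under Randomisation and blinding: "Since the surgical operator and the observer must know which group each subject has been assigned to, they cannot be blinded". The section adds that "the investigators will be aware of the surgical procedures used in the different trial groups", while participants are kept unaware.

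The Objectives section sets the use of the data: "the incidence of adverse events (AEs) and serious adverse events (SAEs) between the two study groups will be compared".

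**The concern.** A randomised comparison of harms is protected only if both arms are counted by the same rule, and that rule does not depend on a judgement that knowledge of the arm can influence. Here the rule is itself such a judgement. Someone must decide that an event is connected with treatment before it counts as an AE, and the trial staff named in the document know which operation was done.

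Expectations could pull that judgement either way. The Introduction describes ultrasonic scalpel haemorrhoidectomy as the safer option and attributes more complications to the Milligan-Morgan operation, which could lower attribution in the test arm. The novelty of the modified technique could raise it. Blinding the statistician does not help, because the statistician sees only the events that passed the definition.

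At stake is the stated safety objective. A difference in AE incidence could reflect how readily events were attributed in each arm, and a real difference could be masked in the same way.

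**Working it through.** **No figure to reproduce.** The protocol article gives no expected AE rate and no sample size for safety. The only input taken from it is 39 patients per arm.

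**Step 1: the sections side by side.**
- Safety section and abstract: an AE must be related to treatment.
- Safety section: researchers and experts evaluate and classify events. Whether the experts are blinded is not stated.
- Randomisation and blinding: operator, observer and investigators know the arm.
- Objectives: AE and SAE incidence is compared between arms.

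Followed as written, the quantity compared is the incidence of events judged related, and the judgement can be made with the arm known.

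**Step 2: what is not exposed.** Secondary outcome measures and Table 1 provide for pain, urinary retention, bleeding (graded 0 to 4, with the top grade needing surgery), oedema, stenosis and continence in both arms, with no relatedness condition. The exposure is confined to other events. Infection is an example: it has no row in Table 1 and is not a listed secondary outcome, although the Rationale and the Discussion both mention incision infection.

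**Step 3: effect of the filter.** Let p be the true event rate, equal in both arms, and let s_T and s_C be the shares judged related in the test and control arms. Then

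recorded risk ratio = (p × s_T) / (p × s_C) = s_T / s_C.

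The true rate cancels. Equal shares give a ratio of 1 whatever their level, so between-arm bias needs s_T and s_C to differ.

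**Step 4: illustration (all shares assumed).** With 10 true events per arm of 39:
- s_T = 0.60, s_C = 0.80: 10 × 0.60 = 6 and 10 × 0.80 = 8, so the ratio is 6/8 = 0.75.
- Shares reversed: 8/6 = 1.33.

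**Step 5: chance of a false significant difference.** Exact enumeration of Fisher's test at two-sided 0.05, 39 per arm, equal true rates of 20%, 40% and 60% (assumed):

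| Share related, control / test | Recorded risk ratio | P(p < 0.05) at 20 / 40 / 60% |
|---|---|---|
| 100% / 100% | 1.00 | 2.8 / 2.8 / 2.8% |
| 90% / 70% | 0.78 | 4.3 / 7.4 / 13.6% |
| 90% / 50% | 0.56 | 10.5 / 26.5 / 49.2% |
| 50% / 50% | 1.00 | 1.6 / 2.8 / 2.8% |

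The last row shows that an equal filter loses events without tilting the comparison. Unequal filters tilt it, and the false-positive chance grows with the gap and with the event rate.

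**The case against.** The strongest reply is that the main expected harms of both operations are collected systematically and carry no causality condition, including bleeding that needs re-operation, and continence at 3 and 6 months. That stands, and it limits the point to the remaining events.

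A reader might infer that only volunteered events are captured. The document does not support this. The text speaks of any spontaneously described event, not of such events alone, and Table 1 has an adverse-event row across the postoperative visits. Because participants are blinded, reliance on volunteering would mainly cause under-ascertainment, not a difference between arms.

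A reader might also infer that the comparison is biased, or that events judged unrelated are certainly never written down. Neither is shown. Judgement before recording follows from the definition but is not stated, and the CRF and the data safety management plan are not shown. Bias needs attribution to differ by arm, and the document gives no rate or direction. In the simplest illustration, 6/39 against 8/39 gives a Fisher p of 0.77, so that example alone would not yield a false significant finding.

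Incision infection might well be judged related, given the Rationale's own reasoning, and could be noticed at the wound checks in weeks 1 to 4. Nor is the loss necessarily permanent: participants are recruited as inpatients, and the monitoring committee checks the CRF against original data. However, an event left off because it was judged unrelated would comply with the definition, so that check need not flag it.

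Finally, the article reports no earlier safety series of the modified operation, but its silence does not establish that none exists.

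**Conclusion.** The point holds in limited form. The article fixes a definition that makes relatedness a condition of being an adverse event, in a trial whose operator, observer and investigators know the arm and whose safety objective is a between-arm comparison of incidence. For events outside the systematically assessed outcomes, that comparison is open to differential attribution of unknown size and direction. The risk ratio of 0.75 (or 1.33 with the shares reversed) and the false-positive chances of 4.3% to 49.2% under unequal shares rest wholly on assumed attribution shares and event rates. They show what the rule permits and do not estimate what has happened. This is a rule stated in the document, not a detail left to a statistical analysis plan.

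**What to change.** - Define an AE as any untoward medical event after randomisation, regardless of cause, and align the abstract's safety sentence with it.
- Hold relatedness and severity as separate CRF fields. Severity is already to be recorded; relatedness moves from the definition to a field, preferably completed by an assessor blinded to arm.
- At each AE visit in Table 1, ask the same open question in both arms, in addition to recording what patients volunteer.
- Compare all-cause AEs and SAEs between arms first, and report treatment-related events as a subset.
- For patients already treated (about two thirds of recruitment was complete according to Trial status), supplement the AE list from hospital notes by the same rule in both arms. This recovers only what the notes contain.

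The cost is an amendment to protocol and CRF wording, somewhat more events to record, and a short chart check. Sample size and the primary analysis are unaffected.

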### Study organisation

#### Data collection and management

The case report form (CRF) includes observation time points, outcome measurements, adverse events, and safety assessments. The evaluators of the results will follow the requirements of the CRF and fill in relevant information in a timely and accurate manner. Data collection and entry will be carried out independently by two staff members and completed by a third staff member. The principal investigator will not be involved in data collection. Data will be obtained from the CRF, and only trial group members will be able to access the CRF and perform dual data entry. The organisation of the test is as follows. The steering committee will fully oversee the design of the study. The Independent Data and Safety Monitoring Committee (IDSMC) will supervise and confirm that the CRF is completed correctly and that the data are consistent with the original data. If there are any errors or omissions, the investigator will immediately correct them. We do not intend to collect personal information about potential or registered participants other than that typically collected during hospitalisation. For confidentiality, the electronic health information will be encrypted in accordance with the hospital’s protocol. After the trial, personally identifiable information will be omitted and placed in a separate database for data analysis.

#### Composition of the data monitoring committee, its role and reporting structure

The Independent Data and Safety Monitoring Committee (IDSMC), consisting of two clinical experts and a statistician, will oversee the safety and quality of the data. This committee is independent and has no competing interests with the research. The IDSMC will consider protocol compliance, trial withdrawal, and safety monitoring and will make recommendations for trial continuation.

#### Statistical analysis

This study is a randomised, single-blind, parallel controlled study. The primary endpoints are the time to incision healing and the time to return to normal activities after modified ultrasonic scalpel haemorrhoidectomy. It can be considered that the recovery time after the treatment of modified ultrasonic scalpel haemorrhoidectomy is approximately normally distributed when testing the superiority hypothesis of modified ultrasonic scalpel haemorrhoidectomy and conventional haemorrhoidectomy. The hypothesis of superiority will be tested in a one-tailed approach, with a *P* value of 0.025 or less considered to indicate statistical significance.

All analyses will be performed with R 4.3.2.

#### Primary efficacy assessments

The primary efficacy measures in this trial are the time to postoperative wound healing and the time to return to normal activity. An equivalence test will be used, and the test hypothesis is as follows:

H0: the recovery time of the intervention group-the recovery time of the control group is ≤ 0;Hα: the recovery time of the intervention group-the recovery time of the control group is > 0.

The recovery time of the two groups will be calculated, and the 95% confidence interval (CI) of the difference between the two groups will be determined. The difference from baseline between the trial group and the control group can be approximated as following a normal distribution, and thus the efficacy analysis will be analysed with the use of T. The superiority hypothesis will be tested between the modified ultrasonic scalpel haemorrhoidectomy group and the conventional haemorrhoidectomy group, and the test *α* = 0.025 (one-sided test). If the *p* value is less than or equal to 0.025, the superiority of postoperative recovery time of the modified ultrasonic scalpel haemorrhoidectomy group compared with the conventional haemorrhoidectomy group will be verified.

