#### Sample size

This study is a randomised controlled trial to evaluate modified ultrasound scalpel haemorrhoidectomy versus the Milligan-Morgan operation for mixed haemorrhoids. According to previous studies [19], the mean value of the experimental group is 10.50, the mean value of the control group is 13.40, and the standard deviation is 3.46 and 3.66, respectively. Two-sided tests is needed, with a test level of 0.05. Using the PASS 15.0 software, the sample size of the two groups is 33, and according to the 15% loss of follow-up, 78 subjects will be expected to be finally collected.

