#### Secondary efficacy assessments

The statistical description and inference of the secondary indicators will be based on the characteristics of the data, and the appropriate descriptive indicators and hypothesis testing methods will be selected.

The comparison of general conditions between the two groups will be analysed by appropriate methods according to the type of indicators. The comparison between the groups of measurement data will be compared by the *t* test (homogeneity of variance, normal distribution) or the Wilcoxon rank sum test according to the distribution of data, and the chi-square test or exact probability method (if the chi-square test is not applicable) will be used for count data. The Wilcoxon rank sum test or stratified chi-square test (CMH test) will used for ranked data. Data analyses will be performed by statisticians who are independent of the study team and who are blinded to the group assignments. The acceptable significance level for all analyses will be *P* < 0.05.

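### The primary hypotheses point the wrong way for a shorter-is-better time, and the test is labelled equivalence although one-sided superiority is intended

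*Protocol article*

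**What the plan says.** All references are to the Protocol article.

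- **Outcomes.** Primary outcome measures names two primary outcomes, incision healing time and time to return to normal activities, both counted in days.
- **Aim of the test.** Statistical analysis says: "The hypothesis of superiority will be tested in a one-tailed approach, with a *P* value of 0.025 or less considered to indicate statistical significance".
- **Label of the test.** Primary efficacy assessments opens differently: "An equivalence test will be used, and the test hypothesis is as follows". No equivalence margin follows.
- **Hypotheses.** The null is "H0: the recovery time of the intervention group-the recovery time of the control group is ≤ 0" and the alternative is "Hα: the recovery time of the intervention group-the recovery time of the control group is > 0".
- **Decision rule.** The same section continues: "If the *p* value is less than or equal to 0.025, the superiority of postoperative recovery time of the modified ultrasonic scalpel haemorrhoidectomy group" over the conventional operation is taken as verified. It also asks for a 95% confidence interval for the group difference and describes the quantity analysed as a change from baseline.
- **Planning values.** Sample size states that "the mean value of the experimental group is 10.50, the mean value of the control group is 13.40", with standard deviations 3.46 and 3.66, a two-sided level of 0.05, 33 per group and 78 in total after 15% loss.
- **General level.** Secondary efficacy assessments closes with a sentence beginning "The acceptable significance level for all analyses will be", which sets P < 0.05.

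**The concern.** For a time to recovery, a better operation gives a negative difference (intervention minus control). The written alternative is a positive difference, so it describes a slower operation, while the decision rule credits rejection as superiority of that operation. In a one-sided test the direction is the core of the hypothesis, so this is more than a matter of style.

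The equivalence label is a second contradiction. Equivalence needs a margin on both sides of zero. A null of ≤ 0 against an alternative of > 0 is a one-sided comparison with zero, and the surrounding text calls it superiority.

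The change-from-baseline wording does not fit either: a time that starts at surgery has no preoperative value, and Table 1 marks no preoperative assessment for either time.

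What is at stake is the pre-specified primary decision rule. The protocol has the statisticians work blinded to allocation, so the direction they apply has to come from the written plan. If the sign is put right only after the results are known, it will look like a post hoc change to the primary test.

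**Working it through.** **Step 1: direction, from the text alone.**

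| Element | Where | Meaning |
|---|---|---|
| Times in days | Primary outcome measures | smaller is better |
| H0: I − C ≤ 0 | Primary efficacy assessments | new operation as fast or faster |
| Ha: I − C > 0 | Primary efficacy assessments | new operation slower |
| p ≤ 0.025 means superiority | Primary efficacy assessments | rejecting H0 credited to the new operation |

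The last two rows cannot both stand with the first. This conclusion needs no numbers.

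**Step 2: reproduce the planned sample size.** Inputs from Sample size: means 10.50 and 13.40, SDs 3.46 and 3.66, two-sided 0.05. Power is not stated.

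- Difference, I − C = 10.50 − 13.40 = −2.90.
- Root-mean-square SD = √((3.46² + 3.66²)/2) = √(25.3672/2) = 3.56.
- Two-sample t test (noncentral t): power is 89.4% with 32 per arm and 90.3% with 33. So 33 per arm is reproduced if 90% power is assumed.
- Loss: 33/0.85 = 38.8, rounded up to 39 per arm, 78 in total. This agrees with the protocol.

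**Step 3: the rule as written, at the planning values.** Assumption: the two means are recovery times in days. The section names neither unit nor endpoint.

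- SE with 33 per arm = √((3.46² + 3.66²)/33) = √0.7687 = 0.877.
- Noncentrality = −2.90/0.877 = −3.31.
- The written rule rejects when T = (I − C)/SE exceeds t(0.975; 64 df), about 2.00.

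| True I − C | Per arm | P(reject, written rule) | P(reject, sign corrected) |
|---|---|---|---|
| −2.90 (planned benefit) | 33 | about 9 × 10⁻⁸ | 90.3% |
| −2.90 | 39 | about 2 × 10⁻⁸ | 94.4% |
| +2.90 (new operation slower) | 33 | 90.3% | about 9 × 10⁻⁸ |
| +2.90 | 39 | 94.4% | about 2 × 10⁻⁸ |

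The normal approximation for the first row, Φ(−(1.96 + 3.31)), gives about 7 × 10⁻⁸. Either way it is of the order of 10⁻⁷, effectively zero. A simulation of 200,000 trials with 33 per arm under the planned benefit gave no rejections with the written rule and 90.3% with the sign corrected.

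**Step 4: one illustrative result.** Suppose the observed difference is exactly −2.90 with 33 per arm. Then t = −3.31 and the two-sided 95% CI is −2.90 ± 2.00 × 0.877 = −4.65 to −1.15. The one-sided p in the written direction is 0.9992; in the intended direction it is 0.0008. The interval shows a clear benefit, while the written test fails to reject.

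**The case against.** The strongest reply is that the intent is plain. Statistical analysis says "The hypothesis of superiority will be tested in a one-tailed approach", the decision rule names superiority of the new operation's recovery time, and the planning means, if they are recovery times, favour the new operation. The required confidence interval would expose a reversed conclusion through its sign. This stands as far as it goes: it is a recoverable error in the formal statement, and it leaves the sample size untouched. A reader might infer that the trial will in fact call a slower operation superior. The documents do not support that as a forecast, because an analyst would have to override all the surrounding text. But recoverable intent does not make the written hypotheses correct. Nor is this detail left to an analysis plan: the hypotheses are given in full, and they are wrong.

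A reader might also infer that the closing P < 0.05 sentence, which speaks of all analyses, doubles the primary type I error from 2.5% to 5%. That does not hold. The sentence ends the secondary section, and the primary level is fixed twice elsewhere at one-sided 0.025. The sample size's two-sided 0.05 has the same critical value as one-sided 0.025. Only a wording note remains.

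Finally, the unit and endpoint behind 10.50 and 13.40 are not given. That limits the probabilities, but not the direction error.

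**Conclusion.** The point holds. The primary hypotheses are stated in the wrong direction for outcomes where fewer days is better, and the equivalence label, with no margin, contradicts the one-sided superiority test at 0.025 that the protocol otherwise specifies. Applied literally, the rule could verify superiority only for a slower operation.

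The size, about 10⁻⁷ under the planned benefit and about 90% if the new operation were 2.9 days slower, rests on three things: literal application, 33 per arm, and the assumption that the planning means are recovery days. The direction error itself rests on none of these assumptions about the planning values. No inflation of the type I error and no fault in the sample size follows from this point.

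**What to change.** In Primary efficacy assessments:

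1. For each of the two primary times, incision healing and return to normal activities, state H0: mean(intervention) − mean(control) ≥ 0 against Ha: mean(intervention) − mean(control) < 0, tested one-sided at 0.025.
2. State that superiority is shown when the upper limit of the two-sided 95% CI for that difference lies below 0.
3. Delete the description as an equivalence test and the reference to a change from baseline.

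As a wording note, limit the P < 0.05 sentence in Secondary efficacy assessments to two-sided tests of secondary outcomes.

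The cost is a few lines of text, submitted as an amendment in the way the protocol already provides for. The sample size, recruitment and data collection do not change. The protocol mentions a statistical analysis plan that is not shown here; check whether it repeats the same hypotheses. Trial status puts recruitment at about two thirds, so at that stage the correction can be made before analysis.
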